The studies by our research group have established knowledge about the development, feasibility, and evaluation of a weighted blanket sleep intervention for children with ADHD and sleep problems. The final phase, implementation, focuses on how the intervention works in clinical practice [31] to ensure that it is feasible, (cost-)effective, transferable, and scalable. The aim of this study protocol is to describe a research project evaluating the real-world effectiveness and implementation of a weighted blanket intervention and standard melatonin treatment in routine clinical practice for children with ADHD and sleep problems. The project focuses on: (1) effectiveness, including changes in sleep-related outcomes, treatment adherence, health-related outcomes, and resource utilization within and across the initial treatment arms during the first 12 months after inclusion, (2) longer-term patterns of treatment use, adherence, treatment changes, sleep, health-related outcomes, and resource utilization during the annual follow-ups, and (3) barriers and facilitators in implementation in routine clinical practice. We hypothesize that the two initial treatment arms will show different patterns of change in sleep-related outcomes during the first 12 months, but that both groups will improve according to the CSHQ total score. Changes in the standard melatonin treatment arm are expected to primarily concern sleep onset, whereas changes in the weighted blanket intervention arm are expected to concern other aspects of sleep, including total sleep time, nightly awakenings, and perceived sleep quality. We further hypothesize that approximately half of the children starting with a weighted blanket will continue using it at the one-year follow-up. The annual follow-ups will be used to describe longer-term patterns of continued use, discontinuation, switching between treatments, and combined use of weighted blankets and melatonin.

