## Methods

### Study design

The research project uses a pragmatic prospective longitudinal cohort design with two initial treatment arms: a weighted blanket intervention and standard melatonin treatment. Treatment selection will be based on family preference and clinical decision-making in routine clinical practice rather than randomization. Child-parent dyads will be followed from baseline to 12 months, with annual long-term follow-ups for an additional nine years. The rationale for the long-term follow-up is to capture children’s development from childhood through adolescence and into young adulthood. The main evaluation of real-world changes in sleep, treatment adherence, health-related outcomes and resource utilization will focus on the first 12 months after inclusion, whereas the annual long-term follow-ups will be exploratory and used to describe longer-term patterns of treatment use, adherence, treatment changes, sleep, health-related outcomes, and resource utilization. Treatment changes may include continued use, discontinuation, switching between treatments, and combined use of weighted blankets and melatonin. The cohort study is combined with a process evaluation and uses a hybrid type 1 effectiveness–implementation approach [32, 33], in which clinical outcomes are the primary focus and implementation outcomes and contextual determinants are explored in parallel. Quantitative, qualitative, and mixed methods will be used.

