Follow-up by healthcare professionals at the ADHD unit will be integrated into the standardized care pathway. At inclusion, they will provide information on available treatment options and support families in initiating the selected treatment. During follow-up, healthcare professionals will discuss treatment use, perceived effects, adherence, and possible difficulties. Decisions about treatment continuation, switching, or combined use of weighted blankets and melatonin will be made in dialogue between the family and healthcare professionals as part of routine clinical practice. The standardized care plan for this group is the following: Parents and adolescents aged 15 years or older are offered a one-day course about ADHD. During the first year, follow-up visits are scheduled four weeks after initiation of new medication, and after six months, regardless of medication use. After the first year, the minimum follow-up is a yearly visit up to age 18, with an additional visit if a new medication is introduced. Any anxiety or depressive episodes will be referred to primary psychiatric care up to age 18 years. More complicated psychiatric issues will be referred to the specialized child and adolescent psychiatric services within the same provider. After age 18, the care will be referred to adult psychiatry. If medication is discontinued for more than one year, regular contact with the unit will end, but care can be reinitiated if needed.

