###### School absence and healthcare consumption

Absence from school and healthcare consumption for the children, such as number of visits to medical doctors, nurses, psychologists, emergency departments and specialist care providers, will be reported by parents. The questions have been used in previous studies [72, 73]. Healthcare consumption also includes clinical registry data from the medical health records of the participating children, including the number of visits to the CAMHS and the ADHD unit, type of visit, healthcare professional involved, and prescribed pharmacological treatment.

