### Data analysis

#### Quantitative methods

Data analysis will be performed using IBM SPSS Statistics software v.28 or later (IBM Corp., Armonk, NY, USA). Continuous data will be presented as means and standard deviations or medians and interquartile ranges, and categorical data as numbers and percentages. Changes over time in continuous outcomes assessed repeatedly, including the primary sleep outcome, additional sleep-related measures, and health-related outcomes, will be analyzed using repeated-measures analysis of variance (R-ANOVA) or repeated-measures analysis of covariance (R-ANCOVA), as appropriate. Analyses to assess real-world effectiveness within and across the initial treatment arms will include the primary sleep outcome, treatment adherence, health-related outcomes, and resource utilization, using appropriate statistical methods, such as t-tests, chi-squared tests, or analysis of covariance (ANCOVA). When appropriate, age, sex, ADHD medication, and level of ADHD symptoms, will be included as covariates in R-ANCOVA or ANCOVA models. Analyses of long-term follow-up will take into account patterns of treatment use and changes over time, including continued use, discontinuation, switching between treatments, and combined use of weighted blankets and melatonin. Differences in resource utilization will be analyzed through non-parametric analyses of individual data. To address the risk of Type I errors due to multiple comparisons across several outcome measures, Bonferroni corrections will be applied where appropriate.

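### Resource utilisation is named under two kinds of analysis, and the specific one, non-parametric, carries no stated adjustment for self-selected arms

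*Protocol article*

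**What the plan says.** The Quantitative methods section deals with resource utilisation twice in one paragraph. The first sentence lists four outcome groups for the effectiveness analyses within and across arms, ending with "health-related outcomes, and resource utilization, using appropriate statistical methods, such as t-tests, chi-squared tests, or analysis of covariance (ANCOVA". The second is specific to this outcome: "Differences in resource utilization will be analyzed through non-parametric analyses of individual data". No non-parametric method is named.

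Between the two, the paragraph says that age, sex, ADHD medication and ADHD symptom level, when appropriate, "will be included as covariates in R-ANCOVA or ANCOVA models". No other analysis is given covariates.

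On allocation, the Study design section states: "Treatment selection will be based on family preference and clinical decision-making in routine clinical practice rather than randomization".

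Table 1 lists resource utilisation as a secondary outcome, but the Background places it in the effectiveness aim: "resource utilization within and across the initial treatment arms during the first 12 months after inclusion". The items are mainly counts: visits, school absence and parental work absence. Parent reports are supplemented by medical records, "including the number of visits to the CAMHS and the ADHD unit". On follow-up of care, the Participants and recruitment section says: "After age 18, the care will be referred to adult psychiatry".

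**The concern.** Two matters meet here. First, a reader cannot tell which analysis gives the main between-arm result for resource utilisation, so the choice could be made after the data are seen. Second, the sentence written specifically for this outcome is the one to which no covariate is attached. With treatment chosen rather than randomised, the arms may differ at baseline in age, symptom level, medication or prior use of care, and each of these can drive visits and absence. An unadjusted comparison then mixes any treatment difference with the difference in who chose what.

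A smaller matter concerns the long-term series. The record-based counts cover CAMHS and the ADHD unit, and care moves to adult psychiatry after age 18. Follow-up lasts ten years from entry at 6–14, so in later years those counts fall partly because participants have left the service.

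**Working it through.** **The plan's own figure.** The only calculated figure is 64 per group for the CSHQ total score (Statistical power section). With a difference of 4 and SD 8, d = 4/8 = 0.50. At two-sided alpha 0.05 and 80% power the normal approximation gives 63, and the t-test calculation gives 63.77, rounded up to 64. The figure reproduces but does not bear on resource utilisation, for which the plan gives no number.

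**Which option carries covariates.**

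| Method mentioned for resource utilisation | Covariates stated? |
|---|---|
| t-test, chi-squared test | No |
| ANCOVA | Yes, when appropriate |
| Non-parametric analysis | No |

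If the specific sentence governs, the between-arm comparison has no stated adjustment. If the general sentence governs, adjustment depends on which example is picked.

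**Size of the problem, on assumed data.**
- From the plan: 150 per arm, two-sided 5% test.
- Assumed: one normally distributed confounder x (SD 1) with mean 0 in one arm and 0.4 in the other; negative binomial visit counts with size parameter 1 and mean exp(1 + 0.4x); no treatment effect.
- Expected mean visits: exp(1 + 0.4²/2) = exp(1.08) = 2.94 in the first arm, and exp(1 + 0.4 × 0.4 + 0.4²/2) = exp(1.24) = 3.46 in the second. The ratio is exp(0.16) = 1.17, so confounding alone produces a 17% difference, about 0.5 visits per child.
- Rejection rates in 1,000 simulated trials: unadjusted Mann-Whitney 16.7%; rank analysis of covariance (Quade) with x as covariate 4.5%. The Monte Carlo standard errors are √(0.167 × 0.833/1000) = 1.2 points and √(0.045 × 0.955/1000) = 0.7 points.

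Adjusting for x, even on ranks, brings the error rate back to about its nominal level. The missing adjustment is therefore the defect, not the use of a non-parametric method.

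**Long-term record-based series.** Assume entry ages spread evenly over the whole years 6 to 14, with ten years of follow-up (12 months plus nine annual follow-ups). A child entering at age a spends max(0, a + 10 − 18) = max(0, a − 8) years at 18 or over. For ages 6 to 14 this is 0, 0, 0, 1, 2, 3, 4, 5, 6, which sums to 21 of 9 × 10 = 90 person-years, or 23%. Entry ages 8 to 14, 7 of 9 or 78%, reach 18 by year 10. No child reaches 18 in the first 12 months.

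**The case against.** **The specific sentence can be read as governing.** The general sentence covers four outcome groups and introduces its tests as examples. This is fair: the text is ambiguous rather than flatly contradictory. But reading it this way selects the analysis with no stated covariates, so it settles the ambiguity and leaves the main defect.

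**An article may leave the method's name to a fuller plan.** True of the name. Here, though, the article states where the covariates go, and the specific analysis for this outcome lies outside that.

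Three stronger readings are tempting, and the document does not support them:
- *Rank tests are planned and cannot adjust.* The plan never says rank, non-parametric methods include bootstrap and permutation, and rank methods can adjust, as the 4.5% figure shows.
- *A between-arm cost analysis is planned and needs mean differences.* The Background's phrase "to ensure that it is feasible, (cost-)effective, transferable, and scalable" describes the general purpose of an implementation phase. Table 2 gives implementation cost a descriptive analysis, and no cost comparison between arms is specified.
- *A non-parametric test would lose power.* Which test has more power depends on the assumed shape of the counts, and the ranking can reverse. The document gives no distribution to settle it.

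**The age-18 point is limited.** The main evaluation covers the first 12 months, the later years are exploratory, and parent-reported use of care supplements the records. Lower use of the unit by a child who has stopped medication can also be real, and care can be reinitiated. All of this stands, so the point applies only to the record-based series after age 18.

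**Conclusion.** The concern holds in limited form. The plan does not say which analysis governs the between-arm comparison of resource utilisation, and the analysis specific to that outcome has no stated adjustment in arms formed by choice. This should be changed. Its weight is moderate: the outcome is secondary but part of the 12-month effectiveness aim.

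The illustrative size is a false-positive rate of 16.7% instead of 5%. It rests on one confounder shifted by 0.4 SD and on an assumed effect of that confounder on visits. The real imbalance and its direction are unknown, and covariate adjustment removes only confounding by what is measured.

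The record-based point is secondary and exploratory. Its 23% and 78% depend on the assumed even spread of entry ages.

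**What to change.** Replace the non-parametric sentence with one between-arm analysis for the 12-month visit and absence counts: a count regression, for example negative binomial, adjusted for age, sex, ADHD medication, ADHD symptom level and, where collected, baseline use. Report the adjusted mean difference with a bootstrap 95% CI. Keep an unadjusted non-parametric comparison as a sensitivity analysis only.

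For the exploratory long-term record-based series, report CAMHS and ADHD-unit visits up to age 18 and say why, so that leaving the service is not read as falling use. Do not apply an offset for time under the unit's care to school absence or parent-reported visits: these accrue whether or not the child is under the unit. That time also depends on stopping medication, a post-baseline event.

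The cost is a few sentences and modest extra programming, with no new questionnaires or visits. The price is reliance on a model form. Bootstrap intervals can also fall short under heavy skew: with assumed lognormal data and 150 per arm, a percentile interval for an unadjusted mean difference covered 89% instead of 95%. Model fit should therefore be checked and the sensitivity analysis shown beside the main result.

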### Data collection and assessment

The child-parent dyads answer individual questionnaires at baseline (before the intervention starts), at 1-, 3-, and 6-month follow-ups, at 1-year follow-up, and then annually for an additional nine years. Parent-reported measures include both parent self-reports and parent proxy-reports concerning the child. The questionnaires contain questions about sleep problems, everyday function, lifestyle habits, worry and anxiety, ADHD-related symptoms, health-related quality of life, pain, resource utilization, and questions related to the intervention (Table 1). A purposive sample of approximately 20–25 child-parent dyads from each treatment arm will be interviewed individually at 6 and 12 months.

The implementation of the intervention will be evaluated by resource utilization and interviews. Approximately 5–10 individuals from the clinical staff at the ADHD unit will be interviewed individually and/or in focus groups at 6 and 12 months.

**Table 1 Tab1:** Overview of outcome measures

		Child-reported measures	Parent-reported measures	Clinical staff–reported measures
**Sociodemographic variables**			Children: age, gender, country of birth, medical information, siblings, and age of siblings *. Parents: age, gender, country of birth, civil status, educational level, and employment. Partners: age, country of birth, educational level, and employment.	
**Primary outcomes**	Sleep problems		Children’s Sleep Habits Questionnaire (CSHQ) [36, 37] *, **	
	Treatment adherence and treatment changes		Usage of weighted blanket and/or melatonin *	
**Additional sleep-related measures**	Sleep problems	Insomnia Severity Index (ISI) [40] Sleep Self-Report (SSR) [41, 42]	Pediatric Insomnia Severity Index (PISI) [43] *	
**Secondary outcomes**	Everyday function	Child Outcome Rating Scale (CORS) [44] Work and Social Adjustment Scale, Youth version (WSAS-Y) [45]	Outcome Rating Scale (ORS) [46] Work and Social Adjustment Scale, parent version (WSAS-P) [45] * The Brief Child and Family Phone Interview (BCFPI) [47, 48] *	
	Lifestyle habits		Dietary habits, physical activity, screen time and sedentary time (Health Behaviour in School-aged Children (HBSC) survey) [49] *	
	Worry and anxiety	The State-Trait Anxiety Inventory – short form (Short STAI) [50–52]		
	ADHD-related symptoms		The Swanson, Nolan, and Pelham Scale (SNAP-IV parent) [53, 54] *	
	Health-related quality of life	EQ-5D-Y-3 L [55, 56]	EQ-5D-3 L [57, 58]	

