### Statistical power

The primary outcome is the CSHQ total score. In the absence of an established minimal clinically important difference for the CSHQ and robust estimates of the expected effect of melatonin on CSHQ scores, the sample size calculation was based on previous publications from the SLEEP project, including the randomized controlled crossover trial and subsequent analyses of the same cohort [27, 74, 75], together with studies of melatonin interventions using the CSHQ [76, 77]. In the SLEEP project, the baseline mean CSHQ total score was approximately 53, with an SD of approximately 8, and an assumed follow-up mean of 47 was used for the weighted blanket intervention. Studies of melatonin interventions have reported improvements of approximately 10 points, corresponding to an assumed follow-up mean of 43, with an SD of 8 [76, 77]. Based on the assumed follow-up means of 47 and 43 and a common SD of 8, the standardized effect size was estimated as Cohen’s d = (47 − 43)/8 = 0.50. With 80% statistical power and a two-sided alpha of 0.05, 64 participants are required per treatment group. Given the uncertainty in the assumptions underlying the sample size calculation, and to allow for expected attrition, switching between treatments, combined use of weighted blankets and melatonin during the first 12 months, and retention of a sufficient sample for longer-term follow-up analyses, we aim to include 150 children per initial treatment arm, for a total of 300 children.

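### The planned single-step Bonferroni correction across outcome measures is valid but gives away some power; Holm's procedure gives the same error control and rejects at least as much

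*Protocol article*

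**What the plan says.** One sentence under Quantitative methods deals with multiplicity. Its stated purpose is "To address the risk of Type I errors due to multiple comparisons across several outcome measures", and its method is "Bonferroni corrections will be applied where appropriate".

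The surrounding structure is partly fixed elsewhere in the article:

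- The Statistical power section states that "The primary outcome is the CSHQ total score" and sizes the between-arm comparison without any adjustment: "With 80% statistical power and a two-sided alpha of 0.05, 64 participants are required per treatment group".
- The Primary outcomes section and Table 1 also list treatment adherence and treatment changes as primary.
- The Background states a hypothesis that both arms improve on the CSHQ total score.
- Study design places the main evaluation in the first 12 months and calls the annual follow-ups exploratory.
- Below the primary outcomes, Table 1 has a block headed "Additional sleep-related measures" and a long block of secondary outcomes. The secondary block also contains interviews, a staff checklist and implementation costs.

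**The concern.** The named method is the single-step form of Bonferroni, which holds every test to 0.05/m, with m the number of tests in the family. Table 1 is long, so m may be large and the threshold severe. Holm starts at the same threshold and relaxes it after each rejection, without any added assumption about how the outcomes are related. It therefore dominates Bonferroni as a testing procedure. What is at stake is some avoidable loss of power for real differences in the additional sleep-related and secondary outcomes. Control of false positives is not at stake.

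**Working it through.** **The plan's own figure.** "Based on the assumed follow-up means of 47 and 43 and a common SD of 8" gives d = 4/8 = 0.50. The normal approximation gives n = 2(1.960 + 0.842)²/0.50² = 62.8, so 63 per arm. The exact two-sample t calculation gives 64 per arm (power 0.801; 63 gives 0.795). The stated 64 reproduces, and it is at an unadjusted two-sided 0.05.

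**Size of the family (assumption).** The article gives no m. Counting scores from Table 1 and the instrument descriptions: ISI, SSR and PISI (3); CORS, ORS, WSAS-Y and WSAS-P (4); three BCFPI scales (3); Short STAI (1); three SNAP-IV scores (3); EQ-5D index and VAS for child and for parent (4); pain (1); school absence, work absence and healthcare visits (3). That makes 22 before any lifestyle item. I use m = 20 as a round assumption.

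**The two procedures.** Bonferroni rejects each p ≤ 0.05/20 = 0.0025. Holm orders the p-values and compares the i-th smallest with 0.05/(20 − i + 1), stopping at the first failure: 0.0025 for the smallest, 0.05/19 = 0.00263 for the next, and 0.05/10 = 0.005 for the eleventh. Two facts follow. Every Bonferroni rejection is also a Holm rejection. The first step is identical, so the chance of at least one rejection is identical.

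**Bonferroni power in closed form.** Assume 120 per arm (between the 64 required and the 150 planned; no attrition rate is given) and d = 0.4. The expected z is 0.4 × √(120/2) = 3.098, and the two-sided critical value at 0.0025 is 3.023. Power = Φ(3.098 − 3.023) = Φ(0.075) = 0.530.

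**Holm by simulation** (m = 20, 120 per arm, equal correlation 0.4, z-tests, 200,000 runs):

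| True effects of 20 (d = 0.4) | Bonferroni average power | Holm average power | Gain (points) | Holm family-wise error |
|---|---|---|---|---|
| 5 | 0.530 | 0.544 | 1.4 | 0.036 |
| 10 | 0.530 | 0.566 | 3.5 | 0.032 |
| 15 | 0.530 | 0.595 | 6.6 | 0.026 |

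No Bonferroni rejection was lost in any run, and the chance of at least one rejection was equal in every row.

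**Sensitivity.** At 150 per arm with independent outcomes and d = 0.5, average power goes from about 0.904 to 0.915, 0.930 and 0.987 with 5, 10 and 20 true effects. At d = 0.3 it goes from about 0.335 to 0.342, 0.356 and 0.391. With no true effects both methods have the same family-wise error: 0.049 if independent, 0.035 at correlation 0.5.

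**Why the place of CSHQ should be stated.** If the CSHQ comparison were put inside a Bonferroni family of 20, its power at d = 0.50 would fall from 0.801 to 0.403 at 64 per arm and from 0.991 to 0.899 at 150 per arm, and 122 per arm would be needed for 80%. The sizing at 0.05 shows that it is meant to stand outside.

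**The case against.** Bonferroni is valid under any dependence, so nothing in the sentence is wrong. It also has simple simultaneous confidence intervals, which Holm lacks, and that is a fair reason to keep it in a study meant to inform guidelines. Both points stand. They make this a matter of efficiency.

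The gain also depends on many outcomes being truly different. The article assumes d = 0.50 only for CSHQ, which is outside the family, and with few real effects Holm adds about one point. That stands too.

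A reader might infer three stronger criticisms that the article does not support:

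- **That false positives are uncontrolled.** Twenty independent tests with all nulls true and no correction would give at least one false positive with probability 1 − 0.95²⁰ = 64% (54% at correlation 0.3, 42% at 0.5). That is not this plan's error rate, because the plan does correct.
- **That the undefined family is itself a defect.** Which scores, contrasts and time points are counted is detail that an article may leave to the analysis plan, which is not at hand.
- **That Holm would stop the correction being chosen after the results are seen.** Only fixing the family in advance does that, and it would work equally well with Bonferroni.

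**Conclusion.** The point holds as a minor improvement. For hypothesis testing, Holm is never worse than the named method and is somewhat better when several outcomes truly differ: about 1 point of average power with 5 of 20 true effects, 3.5 with 10 and 6.6 with 15. These figures rest on assumed values for the number of tests (20), children per arm (120), correlation (0.4), effect size (0.4) and number of true effects, none of which the article gives for these outcomes. That Holm rejects at least as much at the same family-wise error needs none of those assumptions. The primary CSHQ comparison and the sample size are unaffected.

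**What to change.** Replace the multiplicity sentence with wording to this effect:

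*The between-arm comparison of the CSHQ total score is tested alone at a two-sided 0.05. Treatment adherence remains a primary outcome, and the hypothesis of CSHQ improvement within each arm remains a stated hypothesis; neither is treated as exploratory. The quantitative child- and parent-reported additional sleep-related and secondary scores, compared between arms over the first 12 months, form one family tested with the Holm procedure at 0.05. Interviews, the checklist and implementation costs are not part of this family. Unadjusted confidence intervals are shown.*

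The list of scores, including whether lifestyle items enter one by one, and the one between-arm test per score can be set in the analysis plan before data are examined. Holm works on p-values from any test, so the non-parametric comparisons of resource use fit without change.

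The cost is one sentence and a sort of p-values, with no extra children or data. The downside is the loss of simple simultaneous intervals that match the tests. The text should say that the intervals are unadjusted, so that they are not read as carrying the Holm correction.
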